### Rationale for the trial

Resumption of smoking by initially successful quitters is arguably the greatest public health challenge in smoking cessation. While there are few interventions at present that are known to reduce the risk of relapse to smoking [2], the development of new approaches like AR could be worthwhile. Despite evidence from laboratory studies indicating that attentional bias can be modified in tobacco smokers using AR procedures [26,30] and the success of such tasks on improving clinical outcomes in other addictions [33] and psychopathologies [34], no study has yet explored the clinical application of these procedures in treatment-seeking smokers.

We therefore propose a double-blind randomised controlled trial of multiple sessions of attentional bias retraining in smokers attempting smoking cessation (ARTS). This translational study offers the ability to both examine the benefits of AR on users of stop smoking services and provide findings to aid our understanding on the phenomenon of attentional bias and its relation to craving, withdrawal symptoms, lapses and relapse in smokers attempting to quit.

### Aims and study questions

The aim of the study is to investigate the efficacy of an AR intervention on attentional bias and smoking cessation outcomes in smokers undertaking behavioural treatment. The following study questions will be addressed:

1) Can AR diminish attentional bias in smokers during cessation; are the effects evident across different cognitive bias tasks and different types of stimuli?

We will investigate whether AR – using multiple sessions - can lead to reductions in attentional bias in smokers who are attempting cessation. If retraining is successful, participants should be able to demonstrate that they can divert their attention away from smoking cues on a visual probe task. We expect AR to reduce the degree to which smokers notice smoking cues in their environment because they are trained away from attending to them.

Similarly, if AR shows material reductions on one cognitive bias task, it is plausible that a reduction may be seen on another task measure - such as the pictorial Stroop task - if similar attentional processes are involved. Finally, if AR produces a global change in attentional bias and not just a task-specific change in bias towards smoking cues, then smokers should be able to transfer their ability to divert their attention away from other smoking cues that are not featured in the retraining procedure.

2) Does AR affect urges to smoke, cue-induced craving or withdrawal symptoms in smokers during cessation?

We will investigate the effects of AR on urges to smoke, cue-induced craving and withdrawal symptoms in smokers during their cessation attempt. If AR procedures are capable of reducing exposure by diverting attention away from smoking cues, this in turn could reduce the capacity of these cues to invoke craving and symptoms of withdrawal.

3) Do the effects of AR on attentional bias persist up to 6 months after cessation?

One marker for the success of AR procedures is to evaluate whether they produce enduring effects; this is particularly pertinent if the presence of attentional bias undermines abstinence [35]. As the durability of AR remains unclear at present, we will investigate whether the effects of AR are evident in smokers after their cessation attempt at follow-up assessments.

4) Does AR reduce the likelihood of relapse in smokers attempting cessation?

We will assess whether retraining can reduce the likelihood of relapse in smokers attempting to quit. If the ability to divert attention away from smoking-related cues during retraining translated to a smoker’s natural environment, s/he might experience less exposure to the environmental cues that would normally trigger smoking; in time, this could weaken the stimulus–response association between smoking cues and smoking behaviour, thus reducing the likelihood of a lapse occurring. Alternatively, if attentional avoidance leads to less instances of craving, this may also in turn reduce the likelihood of relapse, given that craving predicts relapse [13,36,37].

## Methods/design

This is a double blind randomised controlled trial. Participants attending a 7-session weekly NHS stop smoking clinic will be individually randomised to either an intervention group consisting of a modified visual probe task with AR or a control group with placebo training (PT). Five sessions of AR or PT will be delivered. Both groups will receive nicotine replacement therapy (NRT) in the form of transdermal nicotine patches and standard withdrawal orientated behavioural support [38].

### Inclusion criteria

Participants will be required to meet the following inclusion criteria to be eligible for enrolment into the trial:

1. Aged 18 years or over.

2. Currently smoke at least 10 cigarettes per day or 12.5 grams of tobacco or have a value of at least 10 parts per million (ppm) for exhaled carbon monoxide (CO).

3. Have normal or corrected-to-normal vision.

4. Informed consent.

5. Are able and willing to complete all study procedures.

### Exclusion criteria

Participants will be excluded if they present with any of the following:

1. A medical condition that prevents them from seeing the computerised images properly, attending to the task, or pressing the keyboard buttons on the computer accurately, or completing any other study procedures.

2. Are currently using nicotine replacement therapy (NRT), bupropion, nortriptyline, mecamylamine, reserpine, or varenicline, or undergoing any treatment for tobacco dependence (e.g. acupuncture) that they are not willing to cease using and instead use study medication.

3. Have previously had severe skin reactions to nicotine patches or severe eczema or other skin diseases that make patch use hazardous or undesirable.

4. Have a severe acute or chronic medical or psychiatric condition or previously diagnosed clinically important renal or hepatic disease, which could increase the risk associated with study participation or could interfere with the interpretation of study results and, in the judgment of the investigator, would make the participant inappropriate for entry into this study.

### Withdrawal criteria

It is standard practice in smoking cessation trials to treat those who fail to attend appointments as having relapsed [39]. Therefore, failure to attend will not be defined as withdrawal from the trial; we consider that the only withdrawals will be those in which the participant has asked to be withdrawn. We expect this in less than 5% of participants. This is standard procedure in smoking cessation studies.

### Participant recruitment

Figure 1 shows the flow of participants through the trial. Participants will be recruited from West Midlands NHS SSS. A letter of invitation and a patient information sheet about the study will be sent from GP practices to patients that are registered on their databases as smokers. The letters will ask those patients who wish to take part in the trial to respond to the study team. In our experience, we anticipate that 5–10% will respond. Staff within the NHS SSS will also write to smokers with a history of failed quit attempts who are on their databases. Preliminary eligibility to participate will be assessed during telephone screening and potential participants will be booked in for an assessment session at the clinic site, similar to that arranged by the NHS SSS. Written informed consent will be obtained from all participants at the first session, which takes place 2 weeks prior to quit day.

**Figure 1 F1:**
[figure not shown]
Flow diagram of participants through trial.

### Staff training

Research nurses and stop smoking advisors (SSAs) will be trained to deliver the intervention. All staff will complete a 2-day NHS stop smoking advisor course. They will also attend a training day in which they will be briefed on the clinical procedure on how to deliver each task and on use of the trial database. Prior to running a clinic, each member of staff will observe a baseline session and week −1 (randomisation) session delivered by the chief investigator. In turn, the chief investigator will observe the first two sessions delivered by each nurse/SSA involved in the study. Regular site visits will be conducted to check that the intervention is being delivered as per protocol.

### Trial procedures

Participants in both trial arms will be seen weekly in clinics from 2 weeks prior to quit day up to 4 weeks post quit day. There are ten clinic sessions in total. Randomisation takes place at the second clinic session, which initiates the first of the 5 weekly AR/PT sessions. Follow up visits take place at 8 weeks and 3 months post quit day, with a final visit arranged at 6 months. Participants will be paid £15 to complete assessments at 3 month and 6 month follow-up sessions, as these are not therapeutic encounters. Participants will be reminded to attend their appointments by telephone or text message. Staff will complete a case report form (CRF) at each clinic visit, which contains a checklist of the trial procedures.

### Randomisation

Participants will be randomised 1:1 to either AR or PT using a computer generated simple randomisation scheme, ordered in random permuted blocks of four. The sequence was generated by the trial statistician and entered on to a dedicated online trial database by an independent programmer in the Primary Care Clinical Research and Trials Unit (PCCRTU) at the University of Birmingham. At 1 week prior to quit day, at the start of the clinic session, the therapist will access the randomisation section of the trial database and click on a button that reveals a letter (‘A’ or ‘B’) to reveal the training task to which the participant is allocated. The training tasks are contained within two folders labelled ‘Training A’ or ‘Training B’ on the study laptop, which conceals whether the procedure is AR or PT. These folders were labelled by an independent researcher prior to the start of the trial. Thus the participants, therapists and study staff will be blinded to allocation, to minimize the risk of bias.

### Measures

Table 1 displays the treatment and measurement plan for the study. The measures consist of the following:

• A baseline questionnaire to collect information on the demographic and clinical characteristics of participants. Participant age, gender, ethnicity, education and employment status are classified using UK Census 2011 categories [40]. The questionnaire also contains information on smoking history including the Fagerström Test of Nicotine Dependence (FTND) [41], a 6-item measure assessing the severity of nicotine dependence.

• A visual probe task and pictorial Stroop task to assess attentional bias.

• The Mood and Physical Symptoms Scale (MPSS) [42]. This will be administered at the beginning of every session to assess urge to smoke and withdrawal. A modified version of the MPSS will be used in which each of the nine items is rated on a scale from 1–7. Items relating to the strength and frequency of urges can be combined to produce a composite score (MPSS-C); this is also the case for combined mood items (MPSS-M). The MPSS was preferred over other measures such as the Questionnaire of Smoking Urges because of its superiority in predicting treatment outcomes [43,44].

• Exhaled carbon monoxide (CO). Readings will be taken at the beginning of each session to biochemically verify smoking status.

• A visual analogue scale (VAS) to measure cue-induced craving at the beginning of the second session and following attentional bias assessments. Measurements will be recorded on a 100 mm scale from “Not At All” to “Extremely” prior to and after the task.

• Ecological Momentary Assessment (EMA) [45] to collect information on lapses. EMA is an approach to collecting data in real-time on hand-held electronic devices; it does not carry the risk of recall bias like paper diaries [46]. Participants will be given an electronic diary at the first session and they will be instructed to record any lapses that occur and the circumstances in which the lapse occurs up to 5 weeks post quit day. Those who use an electronic diary will be paid up to £75 at the 8-week session for completing assessments in this way.

• A questionnaire on knowledge of group allocation.

• A patient satisfaction questionnaire developed by the study team on the acceptability of the training tasks. Two items relate to how difficult the task is to understand and carry out, while a further two items assess the convenience of task. Items are rated on a 5-point scale ranging from “not at all difficult” to “extremely difficult” and “very convenient” to “very inconvenient”.

**Table 1 T1:** Treatment and assessment schedule

**Session**	**Treatment**	**Measures**
Baseline (week −2)	Withdrawal-oriented behavioural support	• Baseline questionnaire [demographics, smoking history, Fagerstrom Test for Nicotine Dependence (FTND)]
		• Mood and Physical Symptoms Scale (MPSS)
		• Exhaled carbon monoxide (CO)
		• Attentional bias assessment (visual probe and Stroop tasks)
Pre-quit visit (week −1) Randomisation week	1 week supply nicotine patches Withdrawal-oriented behavioural support Intervention group receives attentional retraining (AR). Control group receives placebo training (PT)	• CO
		• MPSS
		• VAS measure of craving (pre & post cue exposure task)
Quit day (week 0)	1 week supply nicotine patches Withdrawal-oriented behavioural support Intervention group receives AR Control group receives PT	• CO
		• MPSS
Post-quit visits (weeks +1, +2, +3)	1 week supply nicotine patches Withdrawal-oriented behavioural support Intervention group receives AR. Control group receives PT	• CO
		• MPSS
		• Lapses recorded on electronic diary
Week +4 post-quit visit	4 week supply nicotine patches Withdrawal-oriented behavioural support	• CO
		• MPSS
		• Attentional bias assessment (visual probe and Stroop tasks)
		• VAS measure of craving (pre & post cue exposure task)
		• Group allocation assessment
		• Lapses recorded on electronic diary (up to +5 weeks) thereafter reported in clinic CRF
Week +8 post-quit visit	4 week supply transdermal nicotine patches (where eligible)	• CO
		• MPSS
		• Attentional bias assessment (visual probe and Stroop tasks)
		• VAS measure of craving (pre & post cue exposure task)
		• Lapses reported in clinic CRF
3 months post-quit visit		• CO
		• MPSS
		• Attentional bias assessment
		• (visual probe and Stroop tasks)
		• VAS measure of craving (pre & post cue exposure task)
		• Lapses reported in clinic CRF
6 months post-quit visit		• CO
		• MPSS
		• Attentional bias assessment (visual probe and pictorial Stroop tasks)
		• VAS measure of craving (pre & post cue exposure task)
		• Lapses reported in clinic CRF
		• Patient satisfaction questionnaire

### Materials

Eighteen picture pairs of smoking-related and matched neutral pictures will be used across attentional bias assessment and training tasks (picture pairs 1–18). These stimuli have been tested and applied in previous research [47,48]. Each set of pictures consists of a colour photograph of a smoking-related stimulus or scene (e.g. a close-up of a cigarette) matched on age, sex, complexity and ethnicity to another photograph containing no smoking-related content. In the assessment version of the visual probe task and pictorial Stroop task, 12 picture pairs will be used (picture pairs 1–12). Similarly in the AR and PT versions of the visual probe task, the 12 picture pairs consist of 6 picture pairs featured in the assessment version of the task (picture pairs 6–12) in addition to 6 new picture pairs (picture pairs 13–18). An extra 4 neutral picture pairs will be used for practice trials before each task.

### Clinic Tasks

• Visual probe task

• At the baseline session and again at 4 weeks post-quit, 8 weeks, 3 months and 6 months, all participants complete the assessment version of the visual probe task. The assessment version, which will be used to measure attentional bias, comprises a total of 192 trials, presented in two blocks. Each trial begins with a fixation cross displayed in the centre of the computer screen for 500 ms. A picture pair of smoking-related and neutral pictures is then presented side-by-side on the screen for 500 ms. After this picture pair disappears, a visual probe is presented in the location formerly occupied by one of the pictures. This probe is either a circle or square. Participants are required to discriminate the identity of the probe and respond accordingly by pressing the up or down arrow keys on the keyboard as quickly as possible. There is a 500 ms interval before the next trial. Presentation of each picture-pair and probe location is counterbalanced. In all trials, the visual probe replaces the smoking-related and neutral pictures with equal frequency. At the start of the task, participants carry out 8 practice trials in which neutral picture pairs are presented first, to allow them to become familiar with the procedure.

• Each block of trials is presented in a new random order for each participant, using EPrime version 2 (Psychology Software Tools Inc., Pittsburgh PA). The task takes approximately 16 minutes. Attentional bias scores will be calculated from reaction time (RT) data; an attentional bias towards smoking cues is characterized by faster reaction times towards smoking-related pictures than neutral pictures.

• Pictorial Stroop task

• All participants will carry out a pictorial Stroop task as an additional measure of cognitive bias. The pictorial Stroop task will be given after the visual probe task at the baseline session and again at 4 weeks post-quit, 8 weeks, 3 months and 6 months. The task comprises a total of 192 trials, presented in four blocks of 48 trials, with each block consisting of smoking-related pictures or neutral pictures only. Each picture is presented centrally on a computer screen with either an outline of a red, blue, yellow or green border. Participants are required to indicate the colour of the border, while ignoring the picture, by pressing one of four corresponding labelled keys on the keyboard, as quickly as possible. Participants receive 8 practice trials in which neutral pictures are presented first, to allow them to become familiar with the procedure. A short break between blocks will be permitted.

• Each block of trials is presented in a new random order for each participant, using EPrime version 2 (Psychology Software Tools Inc., Pittsburgh PA). The task takes approximately 12 minutes to complete. Stroop bias scores will be calculated from RT data; selective processing of smoking cues is characterized by slower reaction times towards smoking-related pictures than neutral pictures.

• Cue exposure task

• At 1 week prior to quit day, 4 weeks post-quit and follow-up sessions at 8 weeks, 3 months and 6 months, participants in both groups will be given a cue exposure procedure to measure cue-induced craving immediately after completion of the visual probe task and pictorial Stroop task. This is a common procedure in cue-reactivity research [49,50]. Showing a strong craving response to cue-exposure has been shown to predict relapse risk [51]. Prior to attending the session at week −1, participants will be instructed to abstain from smoking for at least 1 hour. We chose an abstinence period of 1 hour to avoid floor effects in craving ratings, commonly found immediately after smoking [52].

• In order to standardize the procedure, instructions for the cue exposure task will be recorded on a digital recorder and then played to participants in the relevant clinic sessions. Before the instructions are played, participants will provide a single rating of their urge to smoke on the VAS. The therapist will place a box that conceals a cigarette and a lighter in front of the participant. The recording will then be played, which instructs the participant to lift up the box and handle the cigarette and lighter contained within. The task lasts 3 minutes. Following the task, participants will provide another rating of their urge to smoke on the VAS.

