• Proportional hazards modelling will be used to analyse the median time to lapse by trial arm; hazard ratios (HRs) will be reported with corresponding 95% CIs. These analyses will be performed using Stata 12.0 (StataCorp, 2011, College Station, TX: StataCorp LP).

• Additional analyses

• We will adjust analyses of attentional bias scores, MPSS-C scores and MPSS-M scores for potential moderators of attentional bias, urge to smoke and withdrawal symptoms. These will include age, gender and FTND across all analyses. Pre-quit urge to smoke will also be examined in the model of attentional bias scores and pre-quit attentional bias in the models of MPSS-C and MPSS-M.

• To investigate longer-term retraining effects, we will analyse 8 week, 3 month and 6 month post-quit data for attentional bias scores using ANCOVA and mixed-effects regression models for MPSS-C scores and MPSS-M scores, as stated previously.

• To examine AR effects on cue-induced craving, VAS scores will be analysed in the same way as MPSS-C and MPSS-M scores, in mixed-effects regression models. Visual analogue scale scores will be calculated from measurements taken from a 0–100 mm scale before and after the cue exposure task, which are administered 1 week before quit day and again at 4 weeks, 8 weeks and 3 months post-quit. The difference between pre and post measurements will be calculated and the change in cue-induced craving over time will be reported.

• Generalisation of AR to other cognitive bias measures will be assessed using RT scores from the pictorial Stroop task. Stroop bias scores will be calculated by subtracting median RTs to probes that replace neutral pictures from median RTs to probes that replace smoking-related pictures. Slower RTs towards smoking-related pictures indicate a bias towards smoking cues. Again, parameters for outlying RTs do not need to be defined as median rather than mean RTs will be used. Bias scores, as measured at 4 weeks post-quit, will be used to examine AR effects on Stroop bias firstly by trial arm and secondly by abstinence status using ANCOVA.

• Similarly, we will assess whether AR generalises to untrained novel stimuli that only appear in the assessment versions of the visual probe task and not during training sessions. Attentional bias scores for the trained and untrained stimuli will therefore be analysed separately using ANCOVAs.

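### At the follow-up visits the pre-cue craving rating comes after two tasks that contain smoking pictures, so any AR effect on picture-evoked craving drops out of the planned contrast

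*Protocol article*

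**What the plan says.** Under Clinic Tasks, the cue exposure procedure at week −1, weeks 4 and 8, and months 3 and 6 is given "to measure cue-induced craving immediately after completion of the visual probe task and pictorial Stroop task". The timing of the first rating is also stated: "Before the instructions are played, participants will provide a single rating of their urge to smoke on the VAS". The cue is a real cigarette and lighter, handled in a task lasting 3 minutes, after which a second VAS rating is given.

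The Measures section places the VAS "at the beginning of the second session and following attentional bias assessments". The second session is week −1. Table 1 lists no attentional bias assessment at that visit, and the description of the visual probe task names only baseline and the four follow-up visits. The general wording under Clinic Tasks, which puts the cue task after both bias tasks at week −1 as well, does not agree with this.

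Under Analysis: "The difference between pre and post measurements will be calculated and the change in cue-induced craving over time will be reported". The outcome appears under Other trial outcomes, defined as the VAS change from before to the end of the cue exposure task.

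Study question 2 asks whether AR affects cue-induced craving. Its reasoning begins: "If AR procedures are capable of reducing exposure by diverting attention away from smoking cues", and goes on to suggest that the cues may then evoke less craving.

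**The concern.** A pre-post difference isolates the effect of a cue when the first rating is taken from a person not yet cued. At the four follow-up visits the first rating comes after two tasks that show smoking pictures, and no earlier VAS rating in the session is described. The pictures are themselves smoking cues, of the kind AR trains people to look away from, and some of the assessment pairs are also used in training (Materials section).

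Two things follow. First, if AR lowers the craving that pictures evoke, the effect is already in the pre-cue rating and is subtracted out. A benefit that study question 2 is meant to detect would go unseen in this outcome. Second, the week −1 reading appears to be taken without prior bias tasks, so change from week −1 reflects the altered task order as well as time.

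**Working it through.** **Exposure before the follow-up pre-cue rating** (inputs from Clinic Tasks)

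- Visual probe assessment: 192 trials; "A picture pair of smoking-related and neutral pictures is then presented side-by-side on the screen for 500 ms"; "The task takes approximately 16 minutes".
- Pictorial Stroop: 192 trials in four blocks, each smoking-only or neutral-only; "The task takes approximately 12 minutes to complete".
- Task time: 16 + 12 = 28 minutes.
- Smoking-picture presentations: 192 + 192/2 = 288. The even Stroop split is an assumption.
- Smoking-picture time is much shorter than 28 minutes: 192 × 0.5 s = 96 s in the visual probe task, always beside a neutral picture, and about 12/2 = 6 minutes of Stroop trials.

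**Effect on the contrast between arms**

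The protocol gives no figure for picture-evoked craving, so every value here is assumed. Let *b* be craving at session start on the 0–100 mm VAS. In a saturating model each cue closes a fraction of the gap to 100: pre = *b* + *p*(100 − *b*) and post = pre + *c*(100 − pre). Take *b* = 40 and *p* = *c* = 0.3; an AR effect cuts the relevant fraction by 30%, to 0.21.

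- PT: pre = 40 + 0.3 × 60 = 58.0; post = 58.0 + 0.3 × 42.0 = 70.6; planned difference 12.6.
- AR acting on both cue types: pre = 40 + 0.21 × 60 = 52.6; post = 52.6 + 0.21 × 47.4 = 62.6; planned difference 10.0.
- AR acting on pictures only: pre = 52.6; post = 52.6 + 0.3 × 47.4 = 66.8; planned difference 14.2.

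In the additive model the pictures and the cigarette each add 12 mm under PT and 8.4 mm where AR acts. AR minus PT, in mm, from unrounded values:

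| Model; where AR acts | Planned (post − pre) | Cue task given first | Post − session start |
|---|---|---|---|
| Saturating; both cues | −2.6 | −5.4 | −8.0 |
| Saturating; pictures only | +1.6 | 0.0 | −3.8 |
| Saturating; cigarette only | −3.8 | −5.4 | −3.8 |
| Additive; both cues | −3.6 | −3.6 | −7.2 |
| Additive; pictures only | 0.0 | 0.0 | −3.6 |

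With *b* from 20 to 60 and *p* from 0.1 to 0.5 in the saturating model, an AR effect on both cues gives a planned contrast that is 15% to 83% of the contrast with the cue task first. If AR acts on pictures only, the planned contrast runs against AR by 0.4 to 3.6 mm. In the additive model the cigarette increment is undistorted, and only the picture-evoked part is missing.

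**Effect on change from week −1**

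Under PT in the saturating model, the rise without prior pictures is 0.3 × 60 = 18.0 mm and the rise after them is 12.6 mm. Cue reactivity would seem to fall by 18.0 − 12.6 = 5.4 mm with nothing changed except task order. In the additive model there is no such shift (12 mm both times). Where the arms react alike, the shift is the same in both and cancels between them.

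**The case against.** The planned difference brackets a 3-minute cigarette cue and matches its definition under Other trial outcomes. A reader might infer that it is not cue-induced craving at all. That goes too far: it measures the response to handling a real cigarette, from a raised starting level. Nor do participants view smoking pictures for 28 minutes; that is the length of two tasks that contain some.

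A reader might also infer that the task order biases the result against AR. The protocol does not support this. Both arms follow the same order, and nothing in it shows how much craving the pictures evoke or whether that differs by arm. The laboratory studies in smokers summarised in the Background gave mixed results on craving. A reversal is easy to construct: start both arms at 30 mm, let the pictures raise PT to 40 and AR to 35, and end at 50 and 47. The total rise is then 20 against 17 mm and the planned difference 10 against 12 mm. But the example assumes that the cigarette adds more under AR (12 mm) than under PT (10 mm), and that assumption produces the reversal. With additive effects and AR neutral or helpful for the cigarette, post minus pre cannot favour PT.

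Two further points carry some weight. A lower primed level under AR would be visible in the recorded pre-cue ratings, but without a session-start VAS it could not be told apart from lower craving on arrival. The MPSS, taken at the start of every session, does give an un-cued urge measure, but its items run from 1 to 7 and it cannot supply the un-cued VAS level. Finally, doing the bias tasks first keeps cigarette handling away from the primary bias measure, which is a good reason to leave the order alone.

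**Conclusion.** The point holds in a limited form. At four visits the pre-cue VAS is a picture-primed rating, whereas at week −1 the Measures section and Table 1 indicate that it is not. The planned contrast therefore omits any AR effect on picture-evoked craving, and change from week −1 mixes time with task order. Attenuation of the cigarette contrast needs ceiling or saturation effects. Reversal needs, in addition, that AR acts wholly or mainly on pictures. The millimetre figures rest on assumed values and show what is possible; the protocol settles neither size nor direction.

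Only an outcome listed under Other trial outcomes is touched. Both primary outcomes and all secondary outcomes stand as planned, and MPSS urge is rated before any task in the session. The change is still worth making, because the un-cued VAS level cannot be recovered later and study question 2 asks about this kind of craving.

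**What to change.** 1. At weeks +4 and +8 and months 3 and 6, add one VAS rating at the start of the session, before the visual probe task. Leave the task order unchanged.
2. Keep the planned pre-post cue-task difference as defined.
3. In the Analysis section, add a supplementary comparison by arm of the picture-evoked change (pre-cue minus session start) and the total change (post-cue minus session start).
4. Reconcile the Measures section, the two task descriptions under Clinic Tasks and Table 1 on whether the bias tasks precede the cue task at week −1, and interpret change from week −1 accordingly.

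The cost is one extra 100 mm mark at four visits and a few lines of analysis text. The total change spans the 28 minutes of tasks as well as the 3-minute cue, so it includes within-session drift and is not like-for-like with week −1. For that reason it should supplement the planned difference and not replace it.
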